### Randomization

A permuted block randomization sequence will be generated by an independent statistician prior to the start of the trial. Eligible patients who consent to study participation will be randomly allocated in a 1:1 ratio in each block to receive either the study intervention or TAU (CG). An investigator who is independent of the patient screening process will be responsible for allocating the patients to the study conditions. Blinding of the patients and rehabilitation professionals is not possible, but the outcome assessors will be blinded to study allocation.

### Study interventions

#### CCT-SE intervention

The CCT-SE intervention will comprise a 10-week manualized group intervention that includes weekly CCT group sessions with three to seven participants, which will be provided by a psychologist at OUH. CCT includes psychoeducation, strategy training, and establishment of new habits in several domains. Patients learn about the natural course of postconcussive symptoms and are introduced to sleep hygiene and stress reduction techniques. Compensatory cognitive strategies are taught regarding organization and prospective memory (task management), attention and concentration (during tasks and social interaction), planning and goal setting, learning and memory (internal and external strategies), and executive function (problem solving and self-monitoring). The CCT manual has been translated into Norwegian and adapted to Norwegian conditions in collaboration with the original author of the manual ([name] [21, 42]). The Norwegian user organization (Personskadeforbundet LTN) has participated in the translation process [43].

The vocational part of the intervention is based on SE principles and will be provided by three trained employment specialists from the NAV Department of Vocational Rehabilitation. For the purpose of this study, the participants will receive vocational intervention for a maximum of 6 months. A main emphasis will be on stages 1 (client engagement), 4 (employer engagement), and 5 (on- and off-the-job support) of the SE Five-Stage Process [38], because all participants will be in regular employment at the time of injury. The initial contact with the participant will be focused on establishing a trustful relationship between the employment specialist and the participant. The employment specialists will use the approach of “discovery,” a process for involving the participant in his/her own RTW process. The next step is mapping the patient’s resources, limitations, and work tasks, as well as establishing common goals between the employment specialist and the participant. The following sessions will be customized to the employee’s needs and may include consultations, guidance and advice, learning/training, work task adaptations, and assistive technology. The sessions may also include the employer and the supervisor at the local NAV office if considered beneficial. The vocational intervention will be integrated with standard Norwegian statutory sick leave follow-up. The International Classification of Health Interventions (ICHI) will be applied for the standardization and documentation of the individualized interventions [44]. ICHI is a tool developed by the World Health Organization for reporting and analyzing health interventions and covers interventions carried out by a broad range of health care providers, including acute care, postacute care, and rehabilitation, as well as assistance with functioning, health prevention, and public health matters. ICHI is still under development, and the last published version is denoted as alpha version 2. The classification will be ready for operational use during the study period.

For the CCT-SE, three NAV employment specialists in the project will follow one group program each to become well acquainted with CCT content and ensure implementation of strategies and compensatory techniques at the workplace. Continuous cooperation between the CCT team, employee, and SE personnel will be emphasized. Employment specialists have participated in formalized postgraduate SE education at Oslo and Akershus University College of Applied Sciences (HiOA). The content of the education is based on the SE Five-Stage Process and the SE Fidelity Scale [37, 38]. Supervision of the employment specialists will be provided by HiOA, with special attention given to discovery, working with employers, on- and off-the-job training, and ongoing support.

The two doctoral candidates in the project will be responsible for provision of the CCT intervention. They are both experienced psychologists and will work in close collaboration with their doctoral program supervisors and the intervention developer ([name]). The feasibility study will ensure adequate training and provide an opportunity to make necessary adjustments to the Norwegian version before inclusion in the RCT.

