### Sample size

Regarding RTW, an OR of 2.0 between the Compensatory Cognitive Training–Supported Employment (CCT-SE) and CG is regarded as the smallest relevant clinical and societal OR. Thus, the required total sample size calculated using G*Power is 110 (i.e., 55 persons in each group; α = 0.05, power level of 0.80) [39]. With an estimated loss to follow-up of 15% [40], 125 participants will be required. On the basis of an ongoing TBI study [41], we assume that this will be achievable within 12–18 months. An OR of 2.0 is equivalent to a 33% absolute difference in employment status between the two groups. According to [name] et al. [21], 50% of patients attained competitive work at 12-month follow-up. If the proportion of employed patients in the CG is 50% at 12-month follow-up, the proportion for the intervention group in this study will be expected to be 83% or above on the basis of the given estimation.

Two strategic samples will be drawn for the process evaluation, comprising 40 cases from the intervention group and 20 from the CG. It is a goal to achieve a heterogeneous sample with variation in severity of TBI, sex, age, type of job and workplace, company size, industry, and sector.

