### Statistical analysis

Descriptive statistics will be used to describe the baseline and injury characteristics of the variables related to participants and services. The *t* test will be used to analyze between-group mean comparisons for normally distributed continuous data, and the Mann-Whitney *U* tests will be used to analyze skewed data. For the primary outcome measures, a logistic regression model will be used to compare the proportions of participants returning to work at T4 in the CCT-SE and TAU groups, adjusting for other potential confounders. In addition, linear regression analysis will be applied to compare the difference in the mean length to RTW between the intervention groups at T4, adjusting for other potential confounders. For the secondary outcome measures, repeated measures analysis of variance will be used with time (T1–T4) as the repeated-measures factor and group (CCT-SE and TAU) being a between-group factor to test whether the CCT-SE intervention has a beneficial effect compared with TAU on RTW, symptoms, and functioning. The intention-to-treat principle will be applied for all proposed analyses.

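### The named between-arm tests ignore that only the CCT-SE arm is nested in CCT groups and employment specialists; if outcomes correlate within these, standard errors are understated

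*Protocol article*

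**What the plan says.** Under Study interventions, CCT-SE intervention, the cognitive part consists of "weekly CCT group sessions with three to seven participants, which will be provided by a psychologist at OUH". The same section states: "The two doctoral candidates in the project will be responsible for provision of the CCT intervention". The vocational part "will be provided by three trained employment specialists from the NAV Department of Vocational Rehabilitation". Under TAU, one multidisciplinary team assesses control patients and follows this with individually tailored services; no treatment groups are described. Under Randomization, individual patients are allocated 1:1.

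Under Statistical analysis, "a logistic regression model will be used to compare the proportions of participants returning to work at T4 in the CCT-SE and TAU groups", with adjustment for other potential confounders. Linear regression is named for time to RTW, repeated-measures ANOVA with time and arm for secondary outcomes, and the t test or Mann-Whitney test for comparisons of continuous data. No term for CCT group, therapist or specialist is named. Sample size gives 110 participants (55 per arm) at "α = 0.05, power level of 0.80", with no allowance for clustering.

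**The concern.** Participants who attend the same CCT group share a therapist, a set of peers and a period of delivery. Those served by the same specialist share that person's skill in working with employers. The article treats the latter as relevant to RTW: its process evaluation asks whether and how specialists build partnerships with employers, and what they contribute to the job match. If outcomes within a group or caseload are alike, the CCT-SE arm holds less information than its head count. A test that assumes independence then understates the variance of the arm difference, and a borderline RTW result would look firmer than it is. The article does not leave the model open. It names a model for each type of outcome, and none of them reflects the delivery structure described a few sections earlier.

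**Working it through.** **The plan's own figure.** The 110 could not be reproduced. At 80% power and two-sided 5%, 50% against 83% needs 31 per arm, and an odds ratio of 2.0 from 50% (that is, 66.7%) needs 137 per arm. That is a separate matter. Here 55 per arm is taken as given.

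**Inputs from the article.** 55 analysed per arm; control RTW 50%; CCT groups of 3 to 7, so about 55/7 ≈ 8 to 55/3 ≈ 18 groups; three specialists, so about 55/3 ≈ 18.3 participants each.

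**Assumed.** ICC of 0.02 to 0.10, since the article gives none; equal cluster sizes; each source of clustering taken alone; each control an independent unit.

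**Formulas.** For cluster size m:
- Design effect in the CCT-SE arm: DE = 1 + (m − 1) × ICC.
- Multiplier on the variance of the arm difference, with equal arms and only one clustered: V = (1 + DE)/2.
- Actual two-sided error of a nominal 5% test: 2 × [1 − Φ(1.96/√V)].

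**Worked cases at ICC 0.05.**
- Groups of 5: DE = 1 + 4 × 0.05 = 1.20; V = 2.20/2 = 1.10; error 6.2%.
- Specialists: DE = 1 + 17.33 × 0.05 = 1.867; V = 2.867/2 = 1.433; error 10.2%. The naive standard error is 1/√1.433 = 84% of the true one.

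**Closed form and simulation.** The simulation column is for RTW of 50% in both arms with beta-binomial clusters in one arm. Rows at ICC 0.05 and 0.10 use a Wald logistic test; the specialist row at ICC 0.02 uses a pooled z-test.

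| Cluster | ICC | DE | V | Closed form | Simulated |
|---|---|---|---|---|---|
| Groups of 3 / 5 / 7 | 0.02 | 1.04 / 1.08 / 1.12 | 1.02 / 1.04 / 1.06 | 5.2 / 5.5 / 5.7% | about 5% |
| Groups of 3 / 5 / 7 | 0.05 | 1.10 / 1.20 / 1.30 | 1.05 / 1.10 / 1.15 | 5.6 / 6.2 / 6.8% | 5.4 / 5.6 / 6.3% |
| Groups of 3 / 5 / 7 | 0.10 | 1.20 / 1.40 / 1.60 | 1.10 / 1.20 / 1.30 | 6.2 / 7.4 / 8.6% | 5.7 / 7.0 / 8.4% |
| Three specialists | 0.02 | 1.35 | 1.17 | 7.0% | 6.5% |
| Three specialists | 0.05 | 1.87 | 1.43 | 10.2% | 9.4% |
| Three specialists | 0.10 | 2.73 | 1.87 | 15.1% | 14.7% |

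With independent participants the Wald logistic test rejects in about 4.5% of simulations, because the data are discrete, so the simulated figures lie a little below the closed form. Repeat simulations moved single cells by up to 0.8 of a point (7.6% against 8.4% for groups of 7 at ICC 0.10).

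**Does a corrected analysis help?** In simulation, a small-sample-corrected cluster-robust test by CCT group holds about 5.0 to 5.5% at every ICC tried, including 0. The same kind of correction applied to three specialists still gives about 6 to 7.5%.

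**The case against.** Five points can be made on the other side.

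- **The inflation is conditional.** A reader might infer that the standard errors are too small and the 5% level is lost as a matter of fact. The documents do not support that. They give no ICC, and at ICC 0 the level is kept. If the intervention changed nobody's outcome, delivery would create no cluster effect. The inflation applies to a null in which the average effect is zero but groups or specialists differ. This stands, and the point is worded accordingly.
- **For CCT groups the effect is modest.** With groups of 3, or at ICC 0.02, it is close to nil. This stands too.
- **The larger figures come from the specialists.** They assume even caseloads and treat the three as a sample from a wider population. The article does not say how participants are assigned, and the specialists share training and supervision. Whether to generalise beyond these three is a choice of inference target. This stands, but that choice should be stated.
- **Random-effect details may be in an analysis plan that is not shown.** That is possible. The article nonetheless names its models, and a plan with cluster terms would have to depart from them.
- **The scope is limited.** One might read the point as covering every analysis. It does not: the health economic section names no regression model, and the process evaluation is thematic. Nor does the article say that group and specialist identifiers go unrecorded.

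**Conclusion.** The point holds in conditional form. The between-arm tests named under Statistical analysis do not match a design in which one arm only is nested in CCT groups and specialists. If the ICC is above 0, they understate uncertainty. Over the assumed 0.02 to 0.10, the two-sided error rate is about 5 to 8% for CCT groups and about 6 to 15% for the three specialists, given 55 per arm, 50% RTW in both arms and one source of clustering at a time.

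It would be tempting to conclude that modelling CCT group settles the matter. It does not: it deals with the smaller source, and three clusters cannot support a reliable variance for the larger one. Nor does anything in the article show that a positive result would come from one effective group or specialist. The named tests simply could not tell.

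**What to change.** Under Statistical analysis, replace the independent-participant models with partially nested versions:

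- For continuous outcomes other than time to RTW, a random CCT-group effect in the CCT-SE arm only, with small-sample degrees of freedom.
- For RTW and time to RTW, small-sample-corrected cluster-robust errors by CCT group, each control being its own cluster.
- Report the ICC.
- Keep the CCT-group and specialist identifiers in the analysis data.
- Report RTW by employment specialist as a descriptive or sensitivity analysis. State that three specialists are too few to estimate a variance, that the result is conditional on these specialists, and that the error rate over a wider population of specialists is not controlled.

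The cost is two identifiers per participant, slightly more complex models, and somewhat wider intervals when the ICC is above 0.

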#### TAU

The CG will receive TAU, which includes follow-up assessment and treatment provided by the multidisciplinary TBI rehabilitation team at OUH. The team consists of six rehabilitation professionals, thus fulfilling requirements for complex rehabilitation [45]. Patients will undergo a medical examination and assessment of physical, cognitive, and mental health and functioning, followed by individually tailored services. The CG will be followed for 6 months after inclusion. These patients will also receive the Norwegian statutory sick leave follow-up, and the treatment received will be registered and mapped according to the ICHI.

### Statistical analysis

Descriptive statistics will be used to describe the baseline and injury characteristics of the variables related to participants and services. The *t* test will be used to analyze between-group mean comparisons for normally distributed continuous data, and the Mann-Whitney *U* tests will be used to analyze skewed data. For the primary outcome measures, a logistic regression model will be used to compare the proportions of participants returning to work at T4 in the CCT-SE and TAU groups, adjusting for other potential confounders. In addition, linear regression analysis will be applied to compare the difference in the mean length to RTW between the intervention groups at T4, adjusting for other potential confounders. For the secondary outcome measures, repeated measures analysis of variance will be used with time (T1–T4) as the repeated-measures factor and group (CCT-SE and TAU) being a between-group factor to test whether the CCT-SE intervention has a beneficial effect compared with TAU on RTW, symptoms, and functioning. The intention-to-treat principle will be applied for all proposed analyses.

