**Methods/design:**

This study protocol describes an innovative randomized controlled trial in which we will explore the effect of combining manualized cognitive rehabilitation (Compensatory Cognitive Training [CCT]) and supported employment (SE) on RTW and related outcomes for patients with mild to moderate TBI in real-life competitive work settings. The study will be carried out in the southeastern region of Norway and thereby be performed within the Norwegian welfare system. Patients aged 18–60 years with mild to moderate TBI who are employed in a minimum 50% position at the time of injury and sick-listed 50% or more for postconcussive symptoms 2 months postinjury will be included in the study. A comprehensive assessment of neurocognitive function, self-reported symptoms, emotional distress, coping style, and quality of life will be performed at baseline, immediately after CCT (3 months after inclusion), following the end of SE (6 months after inclusion), and 12 months following study inclusion. The primary outcome measures are the proportion of participants who have returned to work at 12-month follow-up and length of time until RTW, in addition to work stability as well as work productivity over the first year following the intervention. Secondary outcomes include changes in self-reported symptoms, emotional and cognitive function, and quality of life. Additionally, a qualitative RTW process evaluation focused on organizational challenges at the workplace will be performed.

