A novel approach to vocational rehabilitation based on the “place-then-train principles” in SE involves support in real-life competitive work settings and is aimed at providing professional services to people with disabilities to help them participate in the competitive labor market [26]. The Five-Step Process describes support activities in the inclusion process: engagement, vocational profiling, job finding, employer engagement, and on-/off-job support. The Individual Placement and Support (IPS) Fidelity Scale is based on eight principles: competitive employment, eligibility based on client choice, integration of rehabilitation and health care services, attention to client preferences, personalized benefits counseling, rapid job search, systematic job development, and time-unlimited and individualized support. SE has not been evaluated in RTW for individuals with TBI in the Norwegian context, but IPS has gained empirical support with positive results in terms of both work inclusion and non-work-related outcomes for people with mental illness [27–29]. SE will be implemented in this RCT in combination with CCT. To determine the feasibility of the proposed interventions and the implementation of procedures in a Norwegian context, a feasibility study will be conducted. In the RCT, the effectiveness of a combined cognitive and vocational rehabilitation intervention compared with treatment as usual (TAU; a nonstandardized rehabilitation provided by a multidisciplinary rehabilitation team) will be evaluated.

The following are the main study hypotheses:Combined CCT and SE will result in a faster RTW and better work stability, as well as reduced postconcussive symptoms and improved cognition, than TAU.Combined CCT and SE will result in reduced emotional distress and improved quality of life compared with TAU.Combined CCT and SE will be a cost-effective alternative compared with the TAU condition.Factors related both to the workplace and to the patient’s motivation for RTW will affect the RTW process.

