## Methods/design

### Study design

The proposed study will be a parallel-group RCT with a mixed method in design. Based on the Standard Protocol Items: Recommendations for Interventional Trials (SPIRIT), the study flowchart, standard protocol items, and SPIRIT checklist are provided in Figs. 1 and 2, and Additional file 1, respectively. Once included, participants will undergo a baseline assessment of cognitive and emotional status (T1), with further assessments immediately following the CCT intervention (3 months after study inclusion [T2]), following the end of SE (maximum 6 months after inclusion [T3]), and 12 months after study inclusion (T4). All study assessments will be conducted at Oslo University Hospital (OUH). A process evaluation will be performed to explore participants’ experiences with the intervention, as well as individual and workplace-related mechanisms of importance in the RTW process. A qualitative evaluation study regarding patient experiences with CCT is also being planned.

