### Outcomes

The primary outcome measures are work participation as measured by the proportion of participants who have returned to work at 12-month follow-up and length of time before return to work (in days), work productivity (hours worked, work-related changes [i.e., reduced productivity, increased supervision, work content changes], and work stability [i.e., sickness absence after initial RTW and throughout the study period]). To provide descriptive information and group comparisons, an IQ estimate (Vocabulary, Similarities, Block Design, and Matrix Reasoning subscales of the Wechsler Adult Intelligence Scale–Fourth Edition) will be included at baseline (T1) only [34].

Postconcussive symptoms and quality of life will be used as secondary outcome measures at all time points (T1–T4), whereas outcome will also be measured in the domains of fatigue, sleep, emotional distress, self-efficacy, and cognition. The instruments that will be applied are listed in Table 1. Neuropsychological evaluation will not be conducted at T2.

**Table 1 Tab1:** Secondary and other outcome measures

Outcome measure	Measures
Secondary outcomes	
Postconcussive symptoms	Rivermead Post-Concussion Symptoms Questionnaire (RPQ) [31]
Quality of life	EuroQol five dimensions (EQ-5D) [48]
	Quality of Life After Brain Injury instrument (Qolibri) [49]
Other outcome measures	
Fatigue	Fatigue Severity Scale (FSS) [50]
Sleep	Insomnia Severity Index (ISI) [51]
Self-reported cognitive functioning	Cognitive Failures Questionnaire (CFQ) [52]
Emotional functioning (anxiety and depressive symptoms, posttraumatic stress symptoms, and self-efficacy)	The Patient Health Questionnaire (PHQ-9) [53]
	Generalized Anxiety Disorder seven-item (GAD-7) scale [54]
	Posttraumatic Symptom Scale (PTSS-10) [55]
	General Self-Efficacy Scale (GSS) [56]
Neuropsychological test measures	
Learning and memory	California Verbal Learning Test–Second Edition (CVLT-II) [57]
Prospective memory	Memory for Intentions Screening Test (MIST) [58]
Processing speed/executive function	Color Word Interference Test from the Delis-Kaplan Executive Function System (D-KEFS) [59]
	Trail Making Test (TMT) from the Delis-Kaplan Executive Function System (D-KEFS) [59]
	Coding from the Wechsler Adult Intelligence Scale–Fourth Edition (WAIS-IV) [34]
	Ruff 2 and 7 Selective Attention Test [60]
	Modified Six Elements Test from the Behavioral Assessment of the Dysexecutive Syndrome (BADS) (to be applied at T4 only) [61]

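### Time to return to work, a primary outcome, is to be compared by linear regression of mean time, with no rule for participants who have no observed time

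*Protocol article*

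**What the plan says.** The abstract makes time to RTW primary alongside the RTW proportion: "The primary outcome measures are the proportion of participants who have returned to work at 12-month follow-up and length of time until RTW". The Outcomes section repeats it as "length of time before return to work (in days"). It serves the opening claim of the first main hypothesis: "Combined CCT and SE will result in a faster RTW and better work stability".

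Statistical analysis assigns two models to the primary outcomes. Logistic regression compares the proportions back at work at T4. For time, "linear regression analysis will be applied to compare the difference in the mean length to RTW between the intervention groups at T4", adjusted for confounders that are not named. T4 is the visit "12 months after study inclusion (T4"), so follow-up ends at about day 365. The same section adds: "The intention-to-treat principle will be applied for all proposed analyses".

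The article mentions no survival method, no censoring and no value for a participant who has not returned. The only remark on distribution, Mann-Whitney for skewed data, does not deal with times that were never observed.

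**The concern.** Linear regression of a mean needs a number for every participant. For those still off work at T4, all that is known is that the time exceeds 365 days. For those lost before returning, it exceeds the day of last contact. The plan then has to do one of two things, and it does not say which.

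- **Leave these people out.** The groups compared are then returners only. Returning is itself an effect of treatment, so this is no longer a randomised comparison, and it conflicts with the intention-to-treat statement.
- **Give them a value**, most naturally day 365. The result is then a mean truncated at 12 months, which can be legitimate but should be declared, and it does not cover people lost early.

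At stake is the claim of faster RTW. The logistic model tests whether people are back at T4, not how soon they came back, so that claim rests on this regression.

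**Working it through.** **The plan's own figure.** None is given for the time analysis. Sample size gives 110 (55 per group) for the RTW proportion, with an odds ratio of 2.0 and rates of 50% and 83%. These inputs do not agree: 50% v 83% is an odds ratio of (0.83/0.17)/(0.5/0.5) = 4.88, whereas an odds ratio of 2.0 from 50% gives 2/(1+2) = 66.7%. That is a separate problem. Here both intervention rates are carried through.

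**How many would lack a time.** With 55 per arm, and 12-month employment as a proxy for having returned:

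- 50% v 83%: 55 × 0.50 = 27.5 controls and 55 × 0.17 = 9.4 intervention, about 37 of 110 (33.5%).
- 50% v 66.7%: 27.5 controls and 55 × 0.333 = 18.3 intervention, about 46 of 110 (41.7%).

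**Expected means under constant hazards (an assumption; the article gives no timing).** With λ = −ln(1 − p) per year:

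- mean among returners = 365 × [1/λ − e^(−λ)/(1 − e^(−λ))]
- restricted mean to day 365 = 365 × (1 − e^(−λ))/λ

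| Rate p | λ | Mean among returners | Restricted mean |
|---|---|---|---|
| 50% | 0.693 | 161.6 days | 263.3 days |
| 66.7% | 1.099 | 149.7 days | 221.5 days |
| 83% | 1.772 | 131.2 days | 171.0 days |

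For 50% v 66.7% the returners differ by 161.6 − 149.7 = 12 days, while the restricted means differ by 263.3 − 221.5 = 42 days. For 50% v 83% the differences are 30 and 92 days.

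**Power for benefit.** Simulation with 55 per arm, 4,000 runs per scenario, follow-up to day 365, no loss to follow-up, two-sided 5% level and unadjusted comparisons (a difference in means is linear regression on group). Three timing patterns were assumed: constant hazards; returns spread evenly over the year in both arms; and the same even spread, with the extra intervention returners coming back on days 180 to 365.

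| Timing | Rates | Returners only | Non-returners set to day 365 | Log-rank, censored |
|---|---|---|---|---|
| Constant hazards | 50 v 66.7% | 7% | 39% | 45% |
| Constant hazards | 50 v 83% | 24% | 96% | 98% |
| Same timing | 50 v 66.7% | 2.5% | 26% | 40% |
| Same timing | 50 v 83% | 2% | 75% | 95% |
| Extra returners late | 50 v 66.7% | 0.4% | 11% | 33% |
| Extra returners late | 50 v 83% | 0.1% | 30% | 89% |

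The Schoenfeld formula agrees with the log-rank figures under constant hazards: 45% at a hazard ratio of 1.58 and 98% at 2.56.

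**Sign reversal (returners only, late pattern, 50% v 83%).** Control returners average 365/2 = 182.5 days. Intervention returners average (0.50 × 182.5 + 0.33 × 272.5)/0.83 = 218 days. The intervention looks 36 days slower although more people are back at work. The wrong direction was significant in 31% of runs. With non-returners set to day 365, the direction was kept in all three patterns at these rates (92, 60 and 31 days in favour of the intervention).

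**The case against.** Four points can fairly be made for the plan.

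**The worse reading is not the only one.** A reader might infer that the plan drops non-returners and so will hide or reverse a benefit. The text does not say that. Comparing groups at T4 under intention-to-treat fits assignment of a T4 value at least as well. With complete follow-up, setting non-returners to day 365 yields exactly a restricted mean, and under constant hazards it costs little power (96% against 98%, 39% against 45%). This stands: the small returner differences and the sign reversal belong only to the returners-only reading.

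**The rates are a proxy.** A reader might infer that the plan expects half of controls never to return. The wording is conditional, "If the proportion of employed patients in the CG is 50% at 12-month follow-up", and concerns employment status at 12 months. Its source is the earlier pilot, where "50% of patients attained competitive work at 12-month follow-up", and whose participants were all unemployed at entry (Background). Here all were employed at injury. Someone who returned and stopped again has a time. This also stands, so the share without a time could be below one third. It does not vanish unless everyone returns.

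**Loss to follow-up.** It would be too strong to say that everyone lost before T4 is unusable. Those who returned first have an observed time. Only those lost before returning do not.

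**The proportion is analysed as well.** Logistic regression comes first, can count non-returners as failures and drives the sample size. That limits the damage, but time to RTW is still listed as primary.

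None of this supplies the missing rule. Nor is this a detail that can be left to an analysis plan: the article names a method, and that method does not fit the outcome.

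**Conclusion.** The point holds: the stated method is wrong for this outcome as written. A primary outcome with unobserved times is assigned a model that requires a value for everyone, and no value or censoring rule is given. On the article's own conditional rates, used as a proxy, about 37 to 46 of 110 would have no time, unequally by arm.

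The harm depends on which reading is applied. Returners-only analysis contradicts the intention-to-treat statement and loses most of the power (about 7% or 24%, against 45% or 98% for log-rank under constant hazards), and it can reverse the sign. Assigning day 365 keeps the direction and loses little power under constant hazards, though more under the other two timings. It remains undeclared and has no valid value for those among the expected 15% loss who leave before returning.

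The existence of the flaw is certain from the text. The sizes rest on assumed timing, 55 per arm, no loss to follow-up in the simulation, and employment at 12 months standing in for having returned.

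**What to change.** Replace the linear regression with a time-to-event analysis of all randomised participants:

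- Time runs from inclusion to first RTW, censored at T4 or at last contact if earlier.
- Kaplan-Meier curves by arm, with a Cox model or log-rank test. Any adjusted model uses the same baseline adjustment as the logistic model, with the covariates named in advance, since the article names none.
- The difference in restricted mean time to RTW at 365 days, with its confidence interval, as the effect in days. This keeps the interpretation the sponsor wanted from a mean.

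The change needs no extra participants or visits. Its cost is that the RTW event must be defined, including how part-time return counts, and its timing recorded for each participant. Outcomes already lists time to RTW in days, so the added burden should be small.
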